### 16S rRNA gene sequencing and bioinformatics of the gut microbiota

In accordance with our protocol, the participants will be instructed to collect and store a sample of the first stool passed at home during the two visits (weeks 0 and 8). Sterile plastic containers with fecal samples will be sent to our nutrition clinic within 1 h after fecal collection. The samples will be transferred to the laboratory on dry ice within 48 h of collection and stored at − 80 °C until DNA extraction. DNA extraction kits (OMEGA Stool DNA Kit) will be used to extract gut bacterial DNA following the manufacture’s protocol. The PCR primer will be designed against the conserved region to target the variable region of the 16S rRNA gene. Microbiome signatures will be generated using the Illumina MiSeq platform barcoded V3–V4 primers targeting a hypervariable region of the 16S rRNA gene. The 16S rRNA gene amplification will employ the V3–V4 region-specific primers: 341F:5′-CCTACGGGNGGCWGCAG-3′ and 805R: 5′-GACTACHVGGGTATCTAATCC-3′. The V3–V4 primers (341F/805R) will be selected for their high taxonomic coverage (90–95% of gut taxa) and compatibility with sequencing platform (300-bp paired-end reads). It has also been proven effective in detecting microbiome shifts among GDM patients [27]. On the Illumina MiSeq platform, 300 bp × 2 paired-end reads will be generated.

After sequencing, paired-end reads will be assigned to samples based on their unique barcode and truncated by removing the index and primier sequences. Paired-end reads will be merged using Fast Length Adjustment of Short reads program (FLASH) [28]. Quality filtering of the raw reads will be performed under specific filtering conditions to obtain high-quality clean tags according to fqtrim [29]. Chimeric sequences were filtered using Vsearch [30]. After dereplication using Divisive Amplicon Denoising Algorithm 2 (DADA2) [31], the feature table and feature sequence will be obtained. A taxonomic classification will be assigned to amplicon sequence variants using the latest SILVA database with taxonomic classification at
>99% confidence [32]. The community composition of gut microbiota will be counted at seven levels: kingdom, phylum, class, order, family, genus, and species. To explore each sample’s bacterial diversity and richness, alpha diversity, including the richness(observed species), Shannon indices, Chao 1, and Simpson indices,will be calculated. Beta diversity analysis will be performed to evaluate differences in the microbial communities among samples. Based on KEGG database, PICRUSt2 software will be applied to predict the functional profiles of the microbial communities and their pathways according to 16S rRNA gene sequencing data [33, 34].

### Pregnancy outcomes

After discharge, investigators will assess maternal and neonatal outcomes. Maternal outcome data collection will include premature delivery, hydramnios, proteinuria, cesarean, gestational age at delivery, postpartum Hemorrhage, and maternal OGTT results after 6 weeks. Neonatal outcomes are mainly related to the length of the newborn, birth weight, neonatal respiratory distress syndrome, Apgar score, and hypoglycemia.

### Adverse events {22}

Adverse events to be monitored include the following: Persistent diarrhea (defined as ≥ 3 loose stools per day for > 2 consecutive days); severe abdominal pain or bloating unresponsive to dose modification; clinically significant constipation (Wexner score ≥ 15 persisting after dietary intervention); confirmed hypersensitivity reactions (including but not limited to rash, angioedema, or dyspnea) attributable to XOS/inulin supplementation; hyperglycemia meeting diagnostic criteria (fasting plasma glucose > 7.0 mmol/L or 2-h postprandial glucose > 11.1 mmol/L on two consecutive measurements); new requirement for insulin therapy initiation; development of obstetric complications (preeclampsia, placental abruption, or other pregnancy-related emergencies); and hospitalization-requiring hyperemesis gravidarum or severe ketosis. Any adverse events should be reported to the researchers immediately. Investigators will also ask participants if they have any discomfort. All adverse events will be recorded in the participant case report forms. Once an adverse event is reported, doctors will assess the patient to determine whether they should be withdrawn from the study. All serious adverse events will be followed until resolution.

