Inulin and xylose oligosaccharides (XOS) are two types of soluble fibers. Only one study investigated the effects of pure inulin supplementation in treating GDM; the decrease in HbA1c in the experimental group was greater than that in the control group, but the difference in the decrease of fasting glucose level between the two groups was not significant [10]. Daily inulin intake may have therapeutic effect on GDM. In another small trial, consuming XOS 6 g/day significantly reduced fasting blood glucose of pregnant women with high risk factors for GDM, but the difference in GDM incidence between the two groups was not statistically significant. It is reported that XOS promotes the proliferation of bifidobacteria at a rate 20 times higher than other functional oligosaccharides. The mechanism underlying these positive effects involve changes in the gut microbiota caused by XOS [11]. As a novel food, XOS is considered safe under the proposed uses and use levels [12]. Previous study reported that no diarrhea episodes occurred on the first day of consumption of 3–5 g/day of XOS, but diarrhea occurrence on the first day of consumption of 10–12 g/day XOS was 18–20% [13]. A survey of Chinese women with GDM during their second trimester revealed that their daily dietary fiber intake was found to be only 11.7 ± 4.7 g, and there remains a significant gap between this and the Chinese Nutrition Society’s recommended daily dietary fiber intake of 30–35 g [14]. Based on the aforementioned evidence, we proposed that supplementing with a mixture of inulin and XOS to meet the recommend dietary fiber intake may have a beneficial therapeutic effect in pregnant women with GDM. However, no clinical studies to date have specially investigated this particular intervention.

Our study is to assess the effects of mixed inulin and XOS (XOS inulin) supplementation on glycolipid metabolism and the gut microbiome. The evidence generated from this trial will inform us whether daily XOS inulin supplementation is a viable new dietary approach to treat GDM.

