### Criteria for discontinuing or modifying allocated interventions {11b}

Participants can withdraw from the trial or modify allocated interventions at any time for any reason. The investigator may discontinue patients from the trial to protect their safety or if they are unable or unwilling to continue with the trial (such as pregnancy occurs during trial participation). If adverse event is reported, doctors will also assess the patient to determine whether they should be withdrawn from the study or modify allocated interventions. The reason for each patient’s withdrawal, especially the occurrence of any adverse events, will be explained in detail.

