## Biological specimen collection, analysis, and storage

### Constipation assessment

Constipation is a common sign in GDM patients, and the outcomes from this trial may be beneficial for alleviating this disorder. Two scales, the Wexner constipation score (WCS) and the Bristol Stool Form Scale (BSFS), are used to assess the severity of constipation and measure stool form [24, 25]. The WCS is a Likert scale that includes eight items: the frequency of bowel movements, difficulty, completeness, pain, time, assistance, failure, and history. Based on the grading of the scale, scores range from 0 (normal) to 30 (severe), and a score of 15 is the cut-off point [26]. The BSFS is a 7-point scale for classifying stool forms into seven categories: separate hard lumps, such as nuts (hard to pass); sausage-shaped but lumpy; similar to sausage but with cracks on its surface; soft blobs with clear-cut edges (passed easily); fluffy pieces with ragged edges, a mushy stool; and watery, no solid pieces (entirely liquid) [25]. These two scales are widely used worldwide in clinical and research settings by doctors, researchers, and patients. Investigators will complete questionnaires based on the latest defecation status of the participants during three visits (weeks 0, 4, and 8).

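### Two named gastrointestinal adverse events are badly defined for comparing arms: pain or bloating depends on response to a dose change, and constipation ignores the week 0 score

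*Protocol article*

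**What the plan says.** All places are in the protocol article.

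- **Adverse events {22}** names three gastrointestinal events: diarrhoea of "≥ 3 loose stools per day for > 2 consecutive days"; and then "severe abdominal pain or bloating unresponsive to dose modification; clinically significant constipation (Wexner score ≥ 15 persisting after dietary intervention". The list is introduced as inclusive. The section adds that investigators ask about discomfort and that every adverse event goes into the case report form.
- **Criteria for discontinuing or modifying allocated interventions {11b}**: "Participants can withdraw from the trial or modify allocated interventions at any time for any reason". After a reported adverse event, doctors also assess whether the woman should be withdrawn or her intervention modified.
- **Allocation: sequence generation {16a}**: one arm of 45 receives education only. The fibre arms receive 2 g XOS plus 10 g inulin, or 4 g XOS plus 20 g inulin, daily.
- **Constipation assessment**: constipation is called common in GDM. The Wexner score runs from 0 to 30, "a score of 15 is the cut-off point", and it is taken at weeks 0, 4 and 8. **Outcomes {12}** makes it a secondary outcome.
- **Eligibility criteria {10}** exclude altered gut structure, organic lesions and obstruction, but set no limit on the Wexner score at entry.
- **Background and rationale {6a}** cites "diarrhea occurrence on the first day of consumption of" 10–12 g/day XOS as 18–20%, and no first-day episodes at 3–5 g/day.

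**The concern.** A harm definition used to compare randomised arms should be applicable in each arm and should pick out events that arise after randomisation. Two of the three named events fail one of these tests.

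Symptoms that ease when less product is taken are a typical sign of dose-related intolerance. The pain or bloating definition treats that sign as a reason not to count the case, and it can do so only where there is a product to reduce. The constipation definition cannot tell a woman who became constipated during the trial from one who entered constipated. Because the same score is also an efficacy outcome, the two uses can be confused.

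At stake is the tolerability picture for two doses of a combination that, by the Background section, has not been studied clinically in this population. The trial is open-label, which makes definitions that read the same in every arm more valuable.

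**Working it through.** The plan states no figure on this point, so there is none to reproduce. The check sets the sections side by side and then illustrates the size with assumed rates.

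**1. Pain or bloating, by arm.** In the fibre arms, a severe symptom that responds to dose modification is not a case; one that does not respond is. In the education arm the condition cannot be evaluated. If it is read as unmet, no control woman can ever be a case. If it is ignored there, every severe symptom counts. On either reading the arms are counted by different rules. Within the fibre arms the named event can only fall short of the true number of severe symptoms.

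*Illustration.* Assumptions, none from the protocol: true rates of 25% (fibre) and 5% (control), the condition ignored in control, and a share s of fibre-arm cases settling after a dose change. The n of 45 per arm is the protocol's; alpha is two-sided 0.05.

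Counted fibre rate: p1 = 0.25 × (1 − s), with p2 = 0.05.
Power = Φ{[(p1 − p2) − 1.96·√(2p̄(1 − p̄)/n)] / √[(p1(1 − p1) + p2(1 − p2))/n]}, where p̄ = (p1 + p2)/2.

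For s = 0: p̄ = 0.15; √(2 × 0.15 × 0.85/45) = 0.0753; √((0.1875 + 0.0475)/45) = 0.0723; (0.20 − 1.96 × 0.0753)/0.0723 ≈ 0.73, which gives 77%.

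| s | counted fibre rate | difference (points) | power |
|---|---|---|---|
| 0 | 25.0% | 20.0 | 77% |
| 0.25 | 18.75% | 13.75 | 52% |
| 0.50 | 12.5% | 7.5 | 24% |
| 0.75 | 6.25% | 1.25 | 4% |

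The protocol section describes no test of this event; power is used here only as a scale for the lost contrast.

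**2. Constipation, by baseline status.** A woman who enters at 22 and is at 16 later has improved by 6 points and still meets the criterion. All arms receive dietary advice, so the words about persistence after dietary intervention do not clearly remove her.

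*Dilution.* Let a share b of each arm enter at 15 or more and stay there, and let q be the rate of new constipation in the rest. The counted rate is b + (1 − b)q, so a true difference of q1 − q2 shrinks to (1 − b)(q1 − q2). With assumed q of 20% and 5% (direction arbitrary):

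| b | counted rates | difference (points) | power |
|---|---|---|---|
| 0 | 20% vs 5% | 15 | 57.8% |
| 0.10 | 28% vs 14.5% | 13.5 | 34.5% |
| 0.20 | 36% vs 24% | 12 | 23.5% |

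*Efficacy appearing as safety.* Suppose there is no new constipation at all. If B women per arm enter at 15 or more, and shares rF (fibre) and rC (control) fall below 15, control shows B × (rF − rC) more named events. With rF = 0.5 and rC = 0 (assumed), B = 45 × 0.10 = 4.5 gives 2.25 extra control events, and B = 45 × 0.20 = 9 gives 4.5. No woman was harmed in either arm.

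**3. Diarrhoea (lesser point).** An episode of 1–2 days is not a case; one that starts on day 1 and lasts 3 days is. The rule is the same in all arms, so it costs sensitivity without differing by arm.

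**The case against.** The strongest reply is that this is a list of events to monitor and does not limit what is captured. It is inclusive, discomfort is asked about, all adverse events are recorded, and participants are called weekly. Section {11b} also has the doctor assess modification after an adverse event is reported, so on that route severe bloating is reported before any dose change. Tolerability is not a listed outcome, no test of named event rates is described, and adverse-event tabulation may sit in a plan not shown. Week 0 Wexner scores exist, so existing and new constipation can be separated.

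Much of this stands. It rules out saying that such symptoms are lost from the data. It does not change the wording of the named events: the section does not say whether symptoms below the thresholds count as adverse events, and section {11b} also lets a woman modify her own intervention for any reason.

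Three stronger inferences are tempting, and the document does not support them.

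- *All the distortions favour fibre.* The diarrhoea rule is the same in every arm. Baseline constipation is expected to balance under randomisation and dilutes the contrast; it favours fibre only if fibre relieves constipation.
- *First-day diarrhoea of 18–20% would be missed.* That figure is for 10–12 g/day XOS. The trial gives 2 g or 4 g; the cited result at 3–5 g/day is no first-day episodes, and no rate is given for inulin. The figure describes onset, not duration.
- *A known number of women would be miscounted for constipation.* The protocol calls constipation common but gives no share at 15 or more.

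**Conclusion.** The point holds in limited form. Two named events are badly defined for comparing arms: severe pain or bloating, because its condition cannot be applied in the education-only arm and removes responsive cases in the fibre arms; and constipation, because it takes no account of week 0. If these definitions are tabulated as written, the comparison may be biased or diluted. A reader might go further and conclude that tolerability cannot be compared fairly at all. That is too strong, given the general recording of adverse events and the available baseline scores.

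The size is unknown from the document. The illustrations rest on assumed event rates, assumed shares settling after a dose change and assumed baseline prevalence; they show how the loss behaves, not what it will be. The 2-day diarrhoea threshold is a secondary loss of sensitivity common to all arms. Overall this is a cheap improvement.

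**What to change.** Change the counting rules only; patient management stays as it is.

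1. Remove the dose-response condition from the case definition of abdominal pain or bloating, so that it reads the same in all three arms.
2. Record diarrhoea, abdominal pain and bloating in every arm with onset, duration and severity, including diarrhoea episodes of 1–2 days.
3. Record reduction or stopping of the product for gastrointestinal symptoms as a separate item.
4. Count constipation as an adverse event only when it is new or worse than the week 0 Wexner score, and leave other Wexner change to the secondary outcome.

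The cost is definition wording and a few case-report-form fields; the weekly calls and the Wexner scores at weeks 0, 4 and 8 already exist. The downside is more mild events to record and a higher reported gastrointestinal event rate.

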### Provisions for posttrial care {30}

Posttrial care will continue for 6-week postpartum, during which maternal OGTT results and infant growth/feeding data will be collected via telephone follow-ups. Nutritional counseling will remain available, but XOS inulin supplementation will cease after the 8-week trial period.

### Data collection plan {18a}

Figure 2 shows the baseline and follow-up measurements and a summary of the data. The participant’s follow-up is scheduled for weeks 0, 4, and 8. In weeks 0 and 4, dietary fiber products were dispensed depending on the intervention groups. After obtaining informed consent, baseline assessments will be conducted, including demographics, gestational age, anthropometrics, blood pressure, and heart rate. During this visit, participants will have the first blood test (GSP, fasting glucose, fasting insulin (FINS), 2-h postprandial plasma glucose (2 h-PPG), HbA1c, total cholesterol (TC), LDL cholesterol (LDL-C), HDL cholesterol (HDL-C), and triglycerides (TG)). Trained dietitians will complete the study questionnaire, including a pregnant woman-specific food frequency questionnaire (FFQ), self-reported physical activities, the Wexner constipation score (WCS), and the Bristol stool chart. The same questionnaires and blood tests will be conducted at the second (week 4) and third (week 8) visits. Stool samples will be obtained from participants at every visit to analyze gut microflora colonization patterns. After delivery, information on maternal pregnancy outcomes and neonatal outcomes will be acquired through telephone calls and electronic medical system at the hospital. At 6-week postpartum, we will continue to collect maternal OGTT results and infant growth/feeding data through telephone follow-ups.

**Fig. 2 Fig2:**
[figure not shown]
Standard Protocol Items: Recommendations for Interventional Trials (SPIRIT) schedule for enrollment, treatment, and assessments

### Plans to promote participant retention and complete follow‑up {18b}

Participants will receive a call every week. We will inquire about and document the medication use during telephone visits. Dietitians will also communicate with participants via WeChat at all times to provide real-time assistance. They will also ask participants to document their 24-h dietary intake through photographs at least once a week, and food diaries will be analyzed using dietary analysis software. These approaches will improve participants’ adherence, promote participant retention, and ensure complete follow-up.

### Data management {19}

Research data will be coded as soon as possible using EpiData 3.1. To ensure quality, the data will be entered into EpiData with double-entry verification. Data will be available for researchers internal to the project at Qingdao Municipal Hospital, Department of Clinical Nutrition. They will have access to study protocol, statistical analysis plan, informed consent form, and database.

### Statistical analysis {20a}

Statistical analyses will be performed using the R 4.3.0 software. The Shapiro–Wilk test will be used to check for a normal distribution of the data. Continuous variables with a normal distribution will be presented as the mean (standard deviation [SD]); non-normal variables will be reported as the median (interquartile range [IQR]). Categorical data will be compared among the three groups using chi-square tests and partitions of the chi-square method. Linear models will be used to compare the mean values of the outcome variables among the three groups, adjusting for baseline values (e.g., age, BMI, nationality, gestational weeks, calorific intake). GSP Changes from baseline to week 8 will be analyzed using mixed-effects models with treatment group, time, and group × time interaction as fixed effects, adjusting for baseline GSP. *P*-value of less than 0.05 will be considered statistical significance. Post hoc pairwise comparisons were adjusted using the Bonferroni method to reduce the probability of type I error.

We will evaluate gut microbial diversity through complementary alpha- and beta-diversity analyses. For alpha diversity (within-sample microbial complexity), we will calculate three complementary metrics: Chao1 index (quantifying species richness), Shannon index (reflecting both richness and evenness), and Simpson index (measuring dominance of abundant species). Alpha-diversity differences between groups will be assessed using the Wilcoxon test. The cross-sectional difference in beta diversity (between-sample compositional differences) between the groups will be assessed by permutational analysis of variance (PERMANOVA) of Bray–Curtis dissimilarity and illustrated by PCoA models [35]. The significant bacterial taxa responsible for discrimination between the three groups will be identified via linear discriminant analysis (LEfSe) with linear discriminant analysis (LDA) [36]. Some multiple comparisons, such as differential abundance analysis of the microbiota, will be corrected using the Benjamini–Hochberg false discovery rate (FDR).

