### Explanation for the choice of comparators {6b}

To determine whether a dose–response relationship exists between the dose of XOS inulin and blood glucose metabolism, two supplement doses, 12 g/day and 24 g/day, will be used in the two experimental groups.

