### Trial design {8}

This study is an 8-week, parallel design, open-label, three-arm, single-center randomized controlled superiority trial. The participant flow through the trial is described in Fig. 1. The study protocol was designed and developed in accordance with the Standard Protocol Items: Recommendations for Interventional Trials (SPIRIT) 2013 checklist [15] (see Additional file 1). This trial was registered in the Chinese Clinical Trial registry: ChiCTR2200060117 (May 19, 2022).

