### Sample size {14}

HbA1c monitors the exposure to circulating glycemia in the previous 3 months, whereas glycosylated serum protein (GSP) represents glycemia for 2–3 weeks [17–19]. Because this trial will last for 4 to 8 weeks, we chose the change in GSP as the primary endpoint, which may be more reliable. Since no previous studies assessed soluble fiber supplements for GSP in GDM patients, we calculated the sample size for HbA1c. In an inulin supplementation trial by Miao et al., a difference in HbA1c reduction of 0.27% was observed between the control group and the10 g/day inulin supplemented group [10]. We referred to the results of this trial, showing that an *n* = 37 would provide 90% power at an alpha level of 0.05. Allowing for a 20% dropout, a total sample size of 135 (45 per group) allows for an adequate sample size for our trial.

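### Single-step Bonferroni is valid but more conservative than needed for the three pairwise GSP contrasts: with exactly three arms, Shaffer's step-down keeps 5% family-wise control and loses no rejection

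*Protocol article*

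**What the plan says.** The trial is a "three-arm, single-center randomized controlled superiority trial" (Trial design {8}). To look for dose-response, "two supplement doses, 12 g/day and 24 g/day, will be used in the two experimental groups" (Explanation for the choice of comparators {6b}), and the third arm receives education alone. There are therefore three pairwise contrasts: 12 g against education, 24 g against education, and 24 g against 12 g.

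Statistical analysis {20a} analyses GSP change with "mixed-effects models with treatment group, time, and group × time interaction as fixed effects, adjusting for baseline GSP" and states that a P-"value of less than 0.05 will be considered statistical significance". It closes with "Post hoc pairwise comparisons were adjusted using the Bonferroni method to reduce the probability of type I error". No step-down or closed procedure is named. The count of three contrasts is inferred from the design.

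Sample size {14} rests on a surrogate: "we calculated the sample size for HbA1c". The effect is taken from an earlier inulin trial, where "a difference in HbA1c reduction of 0.27% was observed between the control group and the10 g/day inulin supplemented group", and n = "37 would provide 90% power at an alpha level of 0.05".

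**The concern.** Bonferroni treats the three null hypotheses as if any combination of them could be true. For three means that is not so. If one pair of means differs, the third mean cannot equal both, so at most one of the other two equalities can hold. Once one contrast has been rejected, dividing alpha by three for the rest protects against a situation that cannot occur.

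The cost falls on trials that need more than one contrast. This one does, because its second dose arm is there to study dose-response. At stake is power to show each dose against education, to show both, and to separate a weaker low dose from education. The point concerns the choice of adjustment. That the sample size was computed at an unadjusted 0.05 is a separate matter.

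**Working it through.** **Inputs.** From Sample size {14}: n = 37 per arm, 90% power, alpha 0.05, HbA1c difference 0.27, 20% dropout, 45 enrolled per arm. Assumed: two-sided tests, equal variances, and three week-8 means compared with a pooled variance as a simplification of the mixed model.

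**The plan's own figure.** No SD is given, so n = 37 cannot be checked independently. It does fix the standardised effect d. By the normal approximation, d = (1.960 + 1.282) × √(2/37) = 0.754, so SD = 0.27/0.754 = 0.358. Solving the two-sided t test gives d = 0.764, so SD = 0.27/0.764 = 0.353. Power depends only on d, so the missing SD does not affect the comparison. I use d = 0.764. Evaluable women after dropout: 45 × 0.8 = 36 per arm.

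**Why Shaffer's step-down is valid here.** The rule: test the smallest p at 0.05/3; if it is rejected, test the other two at 0.05. With three means, either all three equalities are true, or exactly one is, or none is.
- All true: an error needs the smallest p to fall below 0.05/3, which has probability at most 3 × 0.05/3 = 0.05.
- One true: an error needs that p-value to fall below 0.05, which has probability at most 0.05.
- None true: no error is possible.

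Any p below 0.05/3 is also rejected by this rule, so no Bonferroni rejection can be lost.

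**Analytic check, n = 36 per arm, 105 df.** The expected t is 0.764 × √(36/2) = 3.241. The critical value is 2.433 at 0.05/3 and 1.983 at 0.05. Approximate per-contrast power is Φ(3.241 − 2.433) = Φ(0.808) = 79% with Bonferroni and Φ(3.241 − 1.983) = Φ(1.258) = 90% unadjusted. Shaffer must lie between the two.

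**Simulation** (400,000 trials per scenario, d = 0.764; gains from unrounded values):

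| Scenario | Quantity | Bonferroni | Shaffer | Gain (points) |
|---|---|---|---|---|
| Both doses at d, n = 36 | each dose | 78.9% | 85.5% | 6.7 |
| | both doses | 67.3% | 80.6% | 13.3 |
| | at least one dose | 90.4% | 90.4% | 0 |
| | false dose-versus-dose claim | 1.7% | 5.0% | – |
| Both doses at d, n = 45 | each dose | 88.2% | 93.0% | about 5 |
| | both doses | 80.6% | 90.1% | 9.5 |
| Low dose d/2, high dose d, n = 36 | low dose | 21% | 35% | 13 |
| | high dose | 79% | 80% | 1 |
| All means equal, n = 36 | any rejection | 4.4% | 4.4% | 0 |

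No Bonferroni rejection was lost under Shaffer in any scenario.

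**Other procedures.** At n = 37 with SD 0.358 and equal doses, Shaffer gains 6.6 and 13.3 points (each dose, both doses), but plain Holm gains only 3.0 and 6.0. An overall F test at 0.05 followed by unadjusted pairs has slightly more power than Shaffer, but it misses a Bonferroni rejection in about 0.1% of trials (equal doses) to 0.4% (half-effect low dose).

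**The case against.** **Bonferroni is not an error.** It is pre-specified, controls the family-wise error and comes with simultaneous intervals that agree with its decisions. This stands: the point is about efficiency. A reader might infer that the planned analysis is invalid or that its type I error is mishandled, and nothing in the protocol supports that.

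**The unused error has some value.** If the two doses are equally effective, Bonferroni makes a false dose-versus-dose claim in about 1.7% of trials and Shaffer in 5.0%. Both are within the 5% limit, but the rate roughly triples on a question the trial was built to ask. This stands as a downside to disclose. The two methods share the same 5% limit. They do not have the same actual error rate in every configuration.

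**The 13 points are conditional.** A reader might take them as a flat loss. They refer to showing both doses, which the protocol does not set as a success criterion: Objectives {7} compares supplementation with education, and Sample size {14} sizes a single comparison. They also assume equal dose effects and 36 evaluable women per arm. The planned adjustment for baseline GSP would shrink them. If it removed 25% of the variance (an assumption), d becomes 0.764/√0.75 = 0.882 and the gains at n = 36 are 4.2 and 8.3 points. The effect size comes from HbA1c, not GSP.

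**Not every sequential method will do.** A reader might infer that any step-down test, or an overall test followed by unadjusted pairs, is equivalent. Holm recovers less than half the gain. The overall-test route can lose Bonferroni rejections and is ambiguous in the planned model: with weeks 4 and 8 as responses, the group-by-time interaction also has 2 df but does not test week-8 differences.

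**Scope.** The Bonferroni sentence follows both the linear models for the other outcomes and the GSP model. Replacing it outright with a week-8 rule would leave other pairwise comparisons with no stated adjustment, so the change should be confined to the primary contrasts.

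**Conclusion.** The point holds as an efficiency improvement to a valid analysis. For the three week-8 GSP contrasts, Shaffer's step-down rejects everything Bonferroni rejects, sometimes more, and keeps strong 5% family-wise control.

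With both doses at d = 0.764 and 36 evaluable per arm, the gain is about 7 points per dose (79% to 86%) and 13 points for showing both (67% to 81%). With all 45 evaluable it is about 5 and 9.5 points. In that equal-dose setting the chance that at least one dose succeeds does not change. If the low dose has half the effect, the gain falls almost entirely on the low dose.

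These figures rest on a standardised effect back-solved from an HbA1c calculation, two-sided tests, three contrasts in the family, and a pooled-variance approximation to the mixed model without baseline adjustment. The logical result, that nothing is lost and 5% control is kept, needs only valid p-values for the three contrasts. It does not depend on the effect size.

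**What to change.** Keep the Bonferroni sentence for other pairwise comparisons and add, before the data are analysed: *For the primary endpoint, the three pairwise group contrasts in GSP at week 8, estimated from the mixed-effects model, will be tested with Shaffer's step-down procedure: the smallest p-value at 0.05/3 and, if it is rejected, the remaining two at 0.05. Simultaneous confidence intervals will be reported at the Bonferroni level.* Do not offer an overall F test followed by unadjusted pairs as an alternative.

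The cost is one sentence and no additional participants. State two downsides alongside it: an interval may include zero for a contrast that the step-down rejects, and if the doses are equally effective the chance of a false dose-versus-dose claim rises from about 1.7% to 5.0%, still within the family-wise limit.
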